The MQT-SH period may vary depending on the setting (9). A manual for researchers and participants was developed to improve compliance to the intervention protocol. In this study, the MQT-SH will be conducted once a week for 1.5 h for a total of six weeks. Each session will consist of 20 min of education, 40 min of practice (i.e., meditation), and 30 min of group activities, such as checking home training and sharing practice experiences. This intervention will be conducted as a group program, with a maximum of 12 people per group. Participants will be asked to perform home training five times a week for at least 30 min each day. Participants will receive guided audio materials for home training. Dropouts will be defined as i) individuals attending three or less out of six sessions, ii) those who complain of physical or psychological discomfort and want to give up because of such discomfort, or iii) those who would want to give up for reasons other than discomfort.

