### Assessment

2.8

Assessments are scheduled at baseline (T1), post-intervention (six weeks; T2), and follow-up (12 weeks; T3). Assessments include observer ratings (conducted by blinded clinicians) and self-report ratings. A structured interview manual will be used to increase the reliability of observer ratings (e.g., 38, 39). If participants drop out, they will not be assessed further. Missing data will be statistically imputed. **Table 2** summarizes the assessment time points.

**Table 2 T2:** Study assessment points.

	Screening	T1	T2	T3
HBDIS	○			
SCID-5	○			
Demographic Information	○			
HS		○	○	○
HCT		○	○	○
HDRS		○	○	○
HARS		○	○	○
STAXI		○	○	○
IVS		○	○	○

T1, baseline; T2, post-intervention; T3, follow-up; HBDIS, Hwa-Byung Diagnostic Interview Schedule; SCID-5, Structured Clinical Interview for DSM-5; HS, Hwabyung Scale; HCT, Hwabyung Comprehensive Test; HDRS, Hamilton Depression Rating Scale; HARS, Hamilton Anxiety Rating Scale; STAXI; State-Trait Anger Expression Inventory; IVS, Integrative Vitality Scale.

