### Statistical analyses

2.13

Analyses based on the Intention-To-Treat (ITT) principle will be conducted, with missing data imputed using expectation-maximization (EM) algorithm.

To investigate the effect of MQT-SH, 2 (group: MQT-SH *vs*. WLC) × 2 (time: T1 *vs*. T2) repeated measures ANOVA will be performed. If the interaction between the group and time is significant, a simple main effect analysis will be performed.

Additional analyses will be performed. First, to investigate the follow-up effect of the MQT-SH, a paired t-test will be performed to compare T3 and T1 and T3 and T2 in the experimental group alone. Second, a paired t-test comparing T3 and T2 in the control group will be performed to investigate the effects of MQT-SH. Third, a subgroup analysis will be performed to investigate the difference in effectiveness depending on the amount of home training. For this purpose, 2 (amount: top 30% *vs*. bottom 30%) × 2 (time: pre-intervention *vs*. post-intervention) repeated-measures ANOVA will be performed. Data from both the experimental and control groups will be used for subgroup analysis.

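### The home-training analysis sets aside about 40% of participants and treats a self-selected, uncontrolled contrast as a difference in effectiveness; it should be a continuous, exploratory association

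*Protocol article*

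**What the plan says.** All of the following is from the Protocol article.

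- **Aim and status.** Section 2.13 introduces a set of secondary looks at the data with "Additional analyses will be performed". The third reads "a subgroup analysis will be performed to investigate the difference in effectiveness depending on the amount of home training".
- **Model.** It is a 2 × 2 repeated-measures ANOVA. One factor is amount (top 30% against "bottom 30%) × 2 (time: pre-intervention" and so on); the other is time. No arm or period factor is mentioned.
- **Data.** "Data from both the experimental and control groups will be used for subgroup analysis". By section 2.1 the MQT-SH arm trains between T1 and T2 and the waiting-list arm between T2 and T3.
- **Exposure.** Section 2.4.1: "Participants will be asked to perform home training five times a week for at least 30 min each day". How much is actually done is up to the participant.
- **Missing outcomes.** Section 2.13 opens with "Analyses based on the Intention-To-Treat (ITT) principle will be conducted, with missing data imputed using expectation-maximization (EM) algorithm" and makes no exception for the home-training analysis. Section 2.8 adds "If participants drop out, they will not be assessed further". Under section 2.4.1, dropouts include "individuals attending three or less out of six sessions" as well as people who choose to give up.

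**The concern.** There are three separate weaknesses.

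1. **Lost information.** An amount measured in enough detail to rank people is reduced to two extreme groups and the middle 40% is not used. In a trial of 64 that is a noticeable loss. Comparing extremes also makes the share of variance explained look larger than it is in the whole sample.

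2. **The label.** People who practise a lot may differ from those who practise little in severity, motivation or attendance. Each person contributes a trained period, so no untreated group is in the comparison. The two arms contribute different calendar periods, the waiting-list arm after six weeks of waiting. A larger improvement among high practisers could reflect any of this. If the result is reported as a difference in effectiveness, readers may take it as a dose effect of home training.

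3. **Imputed outcomes.** People who stop attending probably practise least. If they are ranked and their post-training scores are imputed, part of the low-practice group's change comes from the imputation model and not from measurement.

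**Working it through.** **Inputs from the article.** Total 64, 32 per group; dropout 20%; power 80%; type I error 5%; partial η² 0.04 (section 2.5); the 30%/30% split (section 2.13). **Assumed, because not given:** pre–post correlation 0.5; roughly normal practice amount; linear relation; correlation of 0.3 to 0.5 between practice and the post-training score.

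**Step 1. The plan's own sample size.** f² = 0.04/0.96 = 0.0417. With two time points and correlation 0.5, λ = f² × N × 2/(1 − 0.5) = 0.0417 × 50 × 4 = 8.33, and the non-central F on (1, 48) degrees of freedom gives power 0.807. So 50 is reproduced. Then 25/0.80 = 31.25, rounded up to 32 per group and 64 in total. The 64 and the 20% can be used below.

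**Step 2. Participants not used.** 0.30 × 64 = 19.2, so 19 + 19 = 38 are analysed and 64 − 38 = 26 (40.6%) are not. With 50 completers the figures are 15 + 15 = 30 analysed and 20 (40%) not.

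**Step 3. Information kept.** For the 70th percentile z = 0.524, with normal density 0.348. The mean of the top 30% is 0.348/0.30 = 1.159 SD, so the two groups lie 2 × 1.159 = 2.318 SD apart. Information on a linear slope, relative to using everyone, is 2.318² × 0.30/2 = 0.806, or about 81%.

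**Step 4. Variance explained.** At a correlation of 0.3 the true value is 0.09. In the extreme groups the between-group part is 0.09 × 1.159² = 0.121. The variance of practice in the selected sample is 1 + 0.524 × 0.348/0.30 = 1.608, so total outcome variance is 0.91 + 0.09 × 1.608 = 1.055. The ratio is 0.121/1.055 = 0.115.

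**Step 5. Power without dropout** (simulation, 64 participants, 3,000 runs per setting; the correlation is between practice and the post-training score after allowing for the pre-training score):

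| Assumed correlation | Continuous amount | Top vs bottom 30% |
|---|---|---|
| 0.3 | 0.55 | 0.45 |
| 0.4 | 0.82 | 0.72 |
| 0.5 | 0.96 | 0.90 |

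**Step 6. Imputed cases in the bottom group.** 0.20 × 64 = 12.8, about 13 dropouts. If only people with observed scores are ranked, the share is 0/19 = 0%. If all 13 are ranked and all rank lowest, it is 13/19 = 68%. The same simulation, with regression of post on pre as a stand-in for EM and a correlation of 0.4, gives:

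- All dropouts truly lowest: the top–bottom difference in change falls from 0.80 to 0.40 SD and power from 0.72 to 0.29.
- Dropout unrelated to practice but scored as no training: the difference falls from 0.80 to 0.53 and power from 0.70 to 0.46.
- No true relation: the rejection rate is 0.042 to 0.048, so false positives are not increased.

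**Step 7. The proposed alternative on the same data.** A continuous analysis of observed cases only has power 0.50 in the first dropout setting (against 0.29) and 0.71 in the second (against 0.46).

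**Step 8. Attribution.** No arithmetic applies. Everyone is asked for the same practice, the amount done is not randomised, and both arms enter through their trained period. The contrast lacks what an effectiveness claim needs: a comparator without training, or an allocated dose.

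**The case against.** The strongest case for the plan has four parts.

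- **It is an additional analysis.** The Discussion says the main analysis is the T1–T2 comparison of the randomised groups, and the sample size does not rest on practice amount. This stands and limits the importance of the point.
- **The split still works as a test.** A reader might infer that the analysis cannot show any difference. The figures do not support that: it keeps about 81% of the information under a linear relation, power is reduced and not removed, and the false-positive rate stays near 5%.
- **Dropouts may not be in it.** A reader might also infer that the bottom group will be filled with imputed dropouts. The article does not say so. It does not state what amount a dropout is given, or whether dropouts are ranked. Ranking by practice done is not naturally an intention-to-treat set, controls who leave before T2 never start training, and some dropouts will have practised. The 68% is a ceiling and 0% is equally compatible with the text.
- **The alternative has its own assumptions.** A slope assumes linearity, observed scores make a completer set, and self-selection remains. An arm or period term may simply have been left out of a condensed sentence. All fair, but linearity can be checked, and none of this justifies leaving out the middle 40% or the effectiveness wording.

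The biases also run in opposite directions: extreme groups raise variance explained, while imputation that ignores practice shrinks the contrast. The net direction cannot be stated in advance.

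**Conclusion.** The point holds, as a minor one. The article fixes a method that leaves out about 26 of 64 participants and keeps about 81% of the available information, given a linear relation and roughly normal practice amounts. It then describes as a difference in effectiveness something that can only be an association, because practice is self-selected after baseline, there is no untreated comparator, and two periods are pooled with no stated arm or period term. This part needs no numerical assumption.

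The imputation part is conditional. As written, the EM rule covers this analysis, so between 0% and about 68% of the bottom group could be imputed at 20% dropout, with a pull toward zero. The power figures depend on the assumed correlations and on a simple stand-in for EM. The main randomised comparison is unaffected.

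**What to change.** Replace the top/bottom 30% ANOVA in section 2.13 with one linear model:

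- outcome: post-training score (T2 for the MQT-SH arm, T3 for the waiting-list arm);
- covariates: pre-training score (T1 and T2 respectively), home-training amount as a continuous variable, and arm, which also identifies the period;
- participants: those with an observed post-training score, with no imputed outcomes;
- report: the slope for practice amount with its 95% CI, described as an exploratory association and not as a subgroup effect or a difference in effectiveness.

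Check linearity with a plot or a quadratic term, and state how many participants are excluded for lack of a post-training score.

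**Cost.** Wording of the analysis plan only. The amount must already be recorded in order to rank participants, so no extra participants, visits or measurements are needed. The price is a linearity assumption, which can be checked, and a completer set, whose selection should be acknowledged. Since the trial is already recruiting, the change should be dated and made before outcome data are examined.

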### Sample size

2.5

The sample size was estimated using G*power (37). The sample size calculation is based on a power of 80% and a type I error of 5%, as well as a moderate effect size for the intervention (partial *η*^2^ = 0.04). A minimum sample size of 25 participants per group is estimated (50 participants in total). This number was obtained by performing a simulation procedure using repeated-measures ANOVA, considering the existence of a significant 2 (group: experimental *vs*. control) × 2 (time: T1 *vs*. T2) interaction effect. Considering a dropout rate of 20%, we aim to include 32 participants per group (64 participants in total).

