The control group in this study is a non-active group. For ethical reasons, the control group will perform MQT-SH for six weeks between the T2 and T3 assessments. Therefore, the main statistical analysis is a comparison of the two groups for T1 and T2 assessments. Additionally, a follow-up effect analysis will be conducted in the experimental group alone, and a single-arm pre-post effect analysis will be conducted in the control group. Finally, a subgroup analysis will be conducted based on the amount of home training.

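### The home-training analysis compares only the top and bottom 30%, so it leaves the middle 40% of participants unused on a graded question that all of them could inform

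*Protocol article*

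**What the plan says.** Section 2.4.1 sets home training as a graded quantity: "Participants will be asked to perform home training five times a week for at least 30 min each day". It also makes review of that training part of each session's group time: "30 min of group activities, such as checking home training and sharing practice experiences".

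Section 2.13 introduces a set of secondary looks at the data with "Additional analyses will be performed". The third of these is described as follows: "a subgroup analysis will be performed to investigate the difference in effectiveness depending on the amount of home training". The method is a 2 × 2 repeated-measures ANOVA. One factor is time (before v after the intervention) and the other is "2 (amount: top 30% *vs*. bottom 30" per cent. Both arms are pooled: "Data from both the experimental and control groups will be used for subgroup analysis".

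The Discussion mentions the analysis again ("Finally, a subgroup analysis will be conducted based on the amount of home training") and adds no analysis over the full range of amounts. No reason is given for cutting at 30%.

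**The concern.** The question is graded: does more practice go with more improvement? The planned method turns practice into two extreme groups and leaves out everyone between them. To rank participants into a top and a bottom 30%, the team must hold some measure of amount for every participant, including those left out. The exclusion is therefore a choice of method and is not forced by missing data.

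Two things are at stake. The first is power, in a trial with at most 64 participants. The second is the form of the answer. A contrast between two groups cut at sample percentiles depends on who happens to be in the sample, whereas a slope with a confidence interval uses everyone and states how steep the relation is.

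**Working it through.** **Inputs from the protocol article.** Planned total 64, minimum 50, dropout 20%, and a calculation "based on a power of 80% and a type I error of 5" per cent (section 2.5); tails of 30% with both arms pooled (section 2.13). The distribution of home training and its correlation with improvement are not given, so both are assumed below and shown as ranges.

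**The plan's own figure.** Partial η² = 0.04 gives f² = 0.04/0.96 = 0.0417. For a 2 × 2 within-between interaction with N = 50 and an assumed T1–T2 correlation of 0.5, λ = 0.0417 × 50 × 2/(1 − 0.5) = 8.33 on 1 and 48 df. Power is 0.807, so 50 reproduces. Dropout: 25/0.8 = 31.25, rounded up to 32 per group, or 64 in total. The protocol gives no figure for the home-training analysis.

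**Participants used**
- N = 64: 0.3 × 64 = 19.2, so 19 + 19 = 38 are used and 26 are left out.
- After dropout, 0.8 × 64 = 51.2: 0.3 × 51 = 15.3, so 15 + 15 = 30 are used and 21 are left out.
- At the minimum of 50: 15 + 15 = 30 are used and 20 are left out.

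**Information retained.** The group-by-time interaction in a 2 × 2 repeated-measures ANOVA is the same test as a t-test on change scores. The contrast can therefore be compared with a linear regression of change on amount. With a share p in each tail and tail means D apart, the contrast's information relative to regression on everyone is p × D²/(2 × Var), for a linear relation that is not steep.
- Normal amount: the cut is at z = 0.524. Each tail mean is φ(0.524)/0.3 = 1.159 SD from the centre, so D = 2.318 SD. Relative information = 2.318² × 0.15 = 0.806, a loss of 19.4%.
- Uniform: D = 0.85 − 0.15 = 0.70 and Var = 1/12. Relative information = 0.15 × 0.49 × 12 = 0.882, a loss of 12%.
- Numerically for other shapes: left-skewed beta(5,2) 0.813 (19% lost), gamma with shape 2 0.707 (29% lost), exponential 0.621 (38% lost). A heavier right tail loses more, but a straight line in the raw amount is then harder to believe.

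**Power.** Simulation with 20,000 runs per setting, normal amount, linear relation, two-sided 5%. The continuous analysis is a correlation test of change on amount; the split is a t-test of change between the tails.

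| Assumed correlation | N = 64: continuous v split | N = 50: continuous v split |
|---|---|---|
| 0.30 | 68% v 57% | 57% v 47% |
| 0.35 | 82% v 71% | 72% v 60% |
| 0.40 | 91% v 83% | 84% v 73% |

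The gap is 8 to 12 points throughout.

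**When linearity in the raw amount fails.** Simulation with N = 64, correlation 0.35, a lognormal amount and benefit linear in the log of the amount gives, for raw amount v split: 78% v 72% at log-SD 0.5, 72% v 72% at 0.75, and 66% v 73% at 1.0. Analysing the same data on a log or rank scale keeps power at about 80%.

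**The case against.** The strongest reply has four parts.

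1. The split is a recognised extreme-groups design. For a normal amount it is close to the best equal-tail choice (0.806 at 30% against 0.810 at 27%) and far better than a median split (0.637). It also addresses the question as worded, because the protocol never promises a benefit per minute or a comparison with the prescribed amount. This stands: the plan is neither wrong nor contradictory, only less efficient than it could be.
2. The loss rests on assumptions. The protocol gives neither a distribution nor a correlation, and under strong skew a regression on the raw amount can do no better than the split, or worse. This stands against any unconditional figure and against a fix tied to raw minutes. It does not rescue the split, because an all-participant analysis on a log or rank scale is ahead of it in the skewed cases examined.
3. The protocol does not say that minutes are recorded. Sessions check home training, and an ordering by days practised would be enough to form the tails. This stands, so the fix must not presuppose minutes.
4. Nothing important hangs on the result. The analysis is additional, compares people by how much they chose to practise, and enters neither the hypotheses nor the sample size. This stands and sets the weight of the point.

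A reader might infer that 40% of the information is lost because 40% of participants are. The documents do not support that: the middle of the range says little about a slope, and the loss is about half that share under normality. A reader might also infer that the trial's main conclusion is weakened. It is not, because section 2.13 and the Discussion rest it on the randomised T1–T2 comparison.

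**Conclusion.** The point holds as a low-stakes improvement. That the middle 40% is left out follows directly from the protocol's definition. The size of the loss is conditional: about 19% of the information if the amount is roughly normal and the relation linear, and 12% to 38% across the other shapes tried, given linearity. Under normality and linearity this is roughly 8 to 12 points of power at assumed correlations of 0.30 to 0.40. The power figures describe an unadjusted test on change scores, so they indicate the gain from using everyone and do not predict the exact power of the adjusted model proposed below.

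Neither analysis is protected by randomisation. Using all participants sharpens the estimate but does not show that practice caused the improvement.

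**What to change.** In section 2.13, replace the extreme-group ANOVA by a regression of the post-intervention score on three terms: the pre-intervention score, arm, and amount of home training. Use all participants with data.
- **Pre and post scores:** by the schedule in section 2.1, these are T1 and T2 for the experimental arm and T2 and T3 for the control arm. The arm term therefore also marks the training period, which matters because the arms are pooled.
- **Amount:** enter it in whatever unit is recorded (sessions, days or minutes) and name that unit.
- **Reporting:** give the slope with its 95% CI and check linearity with a plot or a quadratic term. If the amount is strongly skewed, use a log or rank scale.
- **The 30/30 split:** it may stay as a descriptive display.

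The cost is an assumption about functional form, which is checked, and a short protocol change. Section 3.3 says that recruitment and treatment have started, and the Ethics statement sends protocol changes to the IRB, so the change needs that review. It requires no measurement beyond what the planned ranking already needs.

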### Randomization

2.6

Participants will be randomly allocated to either the experimental or the control group (1:1 ratio, block size = 4). Random numbers for allocation will be generated by the computer and managed by the researcher ([name]). Before enrollment, the participants and other researchers will be unaware of the allocation. After enrollment, [name] will allocate participants to the experimental or control group according to random numbers, and the results of the allocation will be shared only with the clinical research coordinator.

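### As written, the general ITT/EM rule keeps dropouts with imputed post scores in the home-training comparison, where they could make up as much as two thirds of the low-training group

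*Protocol article*

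**What the plan says.** Section 2.13 of the protocol article begins with one rule: "Analyses based on the Intention-To-Treat (ITT) principle will be conducted, with missing data imputed using expectation-maximization (EM) algorithm". The randomised group-by-time comparison at T1 and T2 follows, and then three additional analyses. The third compares the 30% who did most home training with the 30% who did least, before and after the intervention. Its only statement about who is included is "Data from both the experimental and control groups will be used for subgroup analysis".

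Two other places bear on this:

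- Section 2.4.1 counts as dropouts those who come to at most three of the six sessions and those who give up, whether for discomfort or another reason.
- Section 2.8 says "If participants drop out, they will not be assessed further", and adds that missing data are imputed.

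Section 2.5 gives the planning figures: "Considering a dropout rate of 20%, we aim to include 32 participants per group (64 participants in total".

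**The concern.** ITT protects a comparison between randomised groups. It protects nothing when the groups are formed by what people did after randomisation, as they are here. Applied to this analysis, the rule brings in people whose outcome was never measured.

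Those people are not spread evenly over the two training groups. Someone who stops the programme will tend to have practised little at home, so low training and a missing post score go together. If EM predicts the missing scores without using training amount, the low trainers receive the change seen in those who carried on, and a real relation is pulled towards zero. If amount is used in a single EM fill-in, the imputed values lie on the fitted line without scatter and are then analysed as if observed, so the test is too ready to find a difference.

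Home practice is a core part of the programme (five times a week, at least 30 minutes), and the article announces this analysis in section 2.13 and twice in the Discussion. A misleading answer in either direction would affect how the programme is taught.

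**Working it through.** **1. The plan's own figures.** Inputs from section 2.5: 80% power, 5% type I error, partial eta squared 0.04, a 2 x 2 interaction. The pre-post correlation is not given; 0.5 is assumed. With f² = 0.04/0.96, noncentrality f² x N x 2/(1 - 0.5) and N - 2 error degrees of freedom, power is 0.791 at N = 48 and 0.808 at N = 50. The stated minimum of 50 is reproduced. Dropout: 25/0.8 = 31.25, rounded up to 32 per group, 64 in total, as stated.

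**2. Share of the bottom group without an observed post score.**

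- Planned dropouts: 0.20 x 64 = 12.8.
- Bottom 30%: 0.30 x 64 = 19.2.
- Ceiling, if every dropout ranks in the bottom group: 12.8/19.2 = 0.67 (13/19 = 0.68 in whole people).
- If three quarters or half of the dropouts rank there: 9.6/19.2 = 0.50 or 6.4/19.2 = 0.33.
- If the 6.4 planned control dropouts all leave while waiting and are not ranked: 6.4/(0.30 x 57.6) = 6.4/17.28 = 0.37.

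**3. Effect on the contrast if amount is not in the EM model.** Assumptions, none from the document: amount and pre score standard normal and independent; slope 0.4 SD of post score per SD of amount; pre-post correlation 0.5; 13 of 64 drop out; top 19 against bottom 19 on change.

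Hand check of the extreme case, in which the 13 lowest trainers drop out:

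- Mean amount in the top 19 of 64 is about 1.165 SD, so the true contrast is 0.4 x 2 x 1.165 = 0.93 SD (0.92 in simulation).
- Mean amount among the 51 observed is about 0.354 SD. The 13 dropouts are in effect given the change belonging to that value.
- The other 6 in the bottom group average about -0.68 SD.
- Apparent bottom-group level: (13 x 0.354 - 6 x 0.68)/19 = 0.03 SD.
- Contrast: 0.4 x (1.165 - 0.03) = 0.45 SD.

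Simulation at 20% dropout:

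| Link between dropping out and low amount | Bottom group imputed | Contrast, EM without amount | Share of 0.92 kept |
|---|---|---|---|
| Dropouts are exactly the lowest trainers | 68% | 0.45 SD | 49% |
| Correlation 0.7 | 48% | 0.61-0.62 SD | 66-67% |
| Correlation 0.4 | 34% | 0.69 SD | 75% |

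**4. Effect if amount is in a single EM fill-in.** The contrast is essentially unbiased: 0.98 of the true value in the extreme case. With a true slope of zero, however, the nominal 5% test rejects in about 9-19% of data sets, most often in the extreme case. The analysis of observed scores rejects in 5-6%.

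**5. The alternative on the same scale.** With only the 51 or so participants who have observed scores, the top-bottom contrast is 0.70-0.89 SD. It is also below 0.92, because removing low trainers narrows the range of training, but every value in it is measured.

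**The case against.** The strongest reply is that the harm depends on matters the article does not fix. It does not list the variables in the EM model, and an article may leave that to an analysis plan. A reader might infer that the stated rule halves the contrast. The documents do not support that: halving needs nearly all dropouts to be the lowest trainers and amount to be absent from the model. Likewise, two thirds is a ceiling and not a forecast. Dropout is partly defined by sessions attended and not by home practice, and controls who leave while waiting have no training to rank. If amount is itself missing for dropouts and is imputed, under 1% of the bottom group are dropouts, although the contrast is still only about 0.67 of its true size.

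The ITT sentence could also be read as meant for the main comparison only. But it stands ahead of all the analyses without restriction, and the home-training analysis has no rule of its own.

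The gain in power from using observed scores is modest outside the extreme case: 63% against 55% at correlation 0.7, 72% against 66% at 0.4, and 51% against 37% in the extreme case. The observed-score analysis is itself safe only if dropout depends on amount and not on outcome, and discomfort is a listed reason for giving up.

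These points limit the size. They do not rescue the rule, because a single EM fill-in misleads whether amount is left out (attenuation) or put in (too many false positives).

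**Conclusion.** The concern holds in a bounded form. Read as written, section 2.13 puts participants with no observed post score into the home-training comparison, mostly on the low-training side. The article's own figures allow up to about two thirds of the bottom group to be imputed; one third to one half is more plausible if dropout is only partly related to training, and 37% is the limit if waiting-phase control dropouts are not ranked. Under the assumed slope and correlation, the cost is either a contrast of 0.61-0.69 SD in place of about 0.92 (0.45 at the extreme) or a false-positive rate of about 9-19%, depending on the EM model.

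A reader might go further and doubt the trial's main result. Nothing here supports that: this is the third of three additional analyses, it is not randomised, and the T1-T2 comparison and the sample size do not depend on it. It is worth correcting because the change is small and the analysis is prominent.

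**What to change.** State in section 2.13 that the ITT/EM rule applies to the randomised T1-T2 comparison. Run the home-training analysis on participants with observed pre and post scores, report how many are excluded in each arm, and limit the conclusion to those assessed.

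If imputation is kept for this analysis, use multiple imputation with home-training amount in the model, and show how many are imputed in each training group. Adding amount to a single EM fill-in is not enough.

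The cost is one or two sentences, about 51 participants and not 64 (64 - 13), and a somewhat narrower range of training in this one additional analysis.
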